### Safety monitoring and adverse events

We are not anticipating any adverse events as part of this intervention; however, we will monitor adverse events during the course of the study. Participants will be asked about any adverse events (including hospital admissions and falls) during all treatment and follow-up visits. All serious adverse events will be recorded and closely monitored until resolution, stabilization or until it has been shown that the study treatment or intervention is not the cause. One investigator (AD) will be informed immediately of any serious adverse events and shall determine seriousness and causality (in conjunction with the medical practitioner steering group representative, if necessary).

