### Intervention and comparator

Participants will be randomized to either usual homecare re-ablement (control group) or the occupational therapy intervention (intervention group). Those randomized to the control group will receive the usual routine care provided by the homecare re-ablement service, that is, a six-week period of homecare re-ablement provided by re-ablement workers (paid care workers), under the direction of a re-ablement care team leader. This does not involve input from qualified health professionals. Therefore, the control group will not routinely receive specialist ADL assessment and intervention, or routinely access community equipment or minor adaptations provided by an occupational therapist as part of their re-ablement package. This is current practice within the sub-team at the trial site. However, if service users in the control group are identified as requiring specific occupational therapy input, they will be referred to the mainstream community occupational therapy team (waiting time currently exceeds the six-week re-ablement period). Referrals to occupational therapy are not routinely made.

Those randomized to the intervention group will receive all routine homecare re-ablement services but, in addition, will receive an enhanced program targeted at ADL, delivered by an occupational therapist. The aim of the enhanced program will be to maximize independence in ADL activities including (but not limited to): washing, dressing, bathing and showering, feeding, indoor mobility, transfers, stair mobility, toileting, meal preparation and kitchen activities, outdoor mobility and community access (as appropriate to individual participants).

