Following the re-ablement service referral, a systematic assessment will be completed by an occupational therapist within five working days. This will identify difficulties the service user may have with ADL due to physical impairments, psychological difficulties or a combination of both. The assessment will be used as a basis to set one or more ADL-related goals for the re-ablement episode. A program will then be agreed with the participant, which will be tailored to the needs of each individual, but will include: practicing activities, and/or a graded process of re-learning and building the skills to manage ADL independently; equipment provision and environmental or activity modification. A case management approach will be adopted by the occupational therapist involving a minimum of weekly reviews and the coordination of the re-ablement episode and other services. Advice and information will also be provided to family members or carers.

The intervention will utilize the occupational therapist’s core skills in activity analysis, where an activity is broken down into its distinct component parts in order to identify the specific element(s) of the task which the individual is unable to perform [24]. The occupational therapist will combine their medical knowledge of prognosis with their assessment of functional ability in order to select an appropriate approach for the re-ablement episode (for example a compensatory or a bio-mechanical approach).

Timely provision of community equipment and/or minor adaptations (such as grab rails, half-steps or threshold removal or replacements) will form a core component of this intervention. These will be prescribed by the occupational therapist and provided by the Community Equipment Service for the local area. The occupational therapist will complete an ongoing review of the use of equipment in order to assess whether the continued use is warranted or no longer required. The enhanced input will continue for the duration of the re-ablement episode (up to six weeks), and will cease when the service user is discharged from the re-ablement service.

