### Compliance

Compliance with the treatment intervention will be monitored by the occupational therapist delivering the intervention. This will be defined as participation in treatment visits and willingness to continue with treatment (further visits).

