### Outcomes

The primary trial outcome will be a determination of the feasibility of conducting a larger, appropriately powered trial. The assessment of feasibility will be a composite measure of recruitment, retention, acceptability and the viability of delivering the intervention. Key aspects to be addressed are: whether the eligibility criteria are realistic, whether service users are willing to be randomized, the dropout rate, the content and scheduling of the occupational therapy treatment visits, the acceptability of the occupational therapy intervention, the most suitable primary outcome measure for the main study and the feasibility of the cost data collection.

The participant outcomes to be assessed will be: personal and extended ADL, health and social care-related quality of life, number of care support hours, health and social care service usage and carer strain. The measures are: Barthel Index (BI), Nottingham Extended Activities of Daily Living (NEADL), Short-Form 36 (SF-36), Adult Social Care Outcomes Toolkit (ASCOT), EQ-5D and Caregiver Strain Index (CSI). Additionally, information will be collected on: number of homecare hours, falls, admissions (to acute and residential services) and use of health and community services. The Mini-Mental State Examination will be completed at the baseline time point in order to provide a description of the sample. The timeline and proposed flow of participants through the study are shown in Figure 1.

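### Adverse events are asked about at therapist visits that only the intervention arm has, so adverse event records are not comparable between arms

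*Protocol article*

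**What the plan says.** The Safety monitoring and adverse events section sets the enquiry rule: "Participants will be asked about any adverse events (including hospital admissions and falls) during all treatment and follow-up visits". It also wants one investigator told at once of any serious event.

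Other sections show what a treatment visit is. Outcomes lists, among the feasibility questions, "the content and scheduling of the occupational therapy treatment visits". Compliance uses attendance at treatment visits to define adherence to the therapist's programme. Intervention and comparator gives the frequency: "A case management approach will be adopted by the occupational therapist involving a minimum of weekly reviews", for a re-ablement episode of at most six weeks. The same section says of usual care, which is all that controls receive: "This does not involve input from qualified health professionals".

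Falls and admissions also appear as participant information under Outcomes: "falls, admissions (to acute and residential services) and use of health and community services". According to the Abstract, participant outcomes are assessed two weeks, three months and six months after discharge from the service. Sample size and recruitment strategy gives the follow-up visits to a masked research assistant. Data collection, management and analysis says that this assistant collects the outcome data in person, and that between-arm differences are calculated at the same three assessments.

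**The concern.** During re-ablement the enquiry differs between arms in three ways: how often it is made, who makes it, and how far back the participant must remember. Intervention participants are asked repeatedly by an unmasked treating therapist. No enquiry is specified for controls until the first follow-up visit. A minor fall in week two may therefore be recorded in one arm and forgotten in the other.

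Any table of adverse events by arm would then mix a true difference with a difference in ascertainment, and the second part runs against the intervention. If the trial's safety picture and event rates inform the definitive study, that distortion goes with them. There is also a practical safety point: the protocol wants serious events reported at once, but for controls it specifies no occasion during re-ablement on which anyone asks.

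**Working it through.** The protocol states no event rate or capture probability, so there is no figure of its own to reproduce. The check counts enquiries and then shows how large the imbalance could be.

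**Enquiries over a full six-week episode**

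- Intervention: 5 or 6 weekly contacts plus 3 follow-up visits = 8 or 9, or more if reviews are more frequent. This treats each weekly review as a visit.
- Control: 3 follow-up visits.
- First specified control enquiry: 6 weeks of re-ablement + 2 weeks = about 8 weeks after starting.
- Share of observation time with unequal enquiry: 6 / (6 + 26) = 19%, taking six months as 26 weeks.

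**Recorded events with no true difference**

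Let p be the probability that a weekly visit captures an event, and q the probability that a follow-up visit captures it by recall. Both are assumptions; the protocol gives neither.

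- Capture in the re-ablement period, intervention: s = 1 - (1 - p)(1 - q). Control: q.
- Capture after discharge: q in both arms.
- Ratio in the re-ablement period: s / q.
- Ratio over 32 weeks: (6s + 26q) / (32q).

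With p = 0.95:

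| q | s | Re-ablement period | 32 weeks |
|---|---|---|---|
| 0.6 | 1 - 0.05 × 0.4 = 0.98 | 0.98 / 0.6 = 1.63 | 21.48 / 19.2 = 1.12 |
| 0.8 | 1 - 0.05 × 0.2 = 0.99 | 0.99 / 0.8 = 1.24 | 26.74 / 25.6 = 1.04 |
| 1.0 | 1.00 | 1.00 | 1.00 |

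A simpler model, in which an intervention event can be captured only at the weekly visit, gives 0.95 / 0.8 = 1.19 to 0.95 / 0.6 = 1.58 for the re-ablement period. Both models give about 1.2-1.6.

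**What 25 per arm would show**

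Assume further 1 event per person-year and q = 0.6.

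- Re-ablement period: 25 × (6/52) × 0.98 = 2.8 expected recorded events in the intervention arm, against 25 × (6/52) × 0.6 = 1.7 in the control arm.
- 32 weeks: 10.3 against 9.2.
- In Poisson simulation the intervention arm had strictly more events in 61% of trials for the re-ablement period and 55% for the whole period. It had strictly fewer in 22% and 36%.

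**After the fix**

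If only events elicited at the three common visits are compared, capture is q in both arms and the expected ratio is q / q = 1.00, provided recall at those visits is equal in both arms.

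**The case against.** The best reply is that the outcome comparison is already protected. A reader might infer from the safety section that the falls and admissions outcomes are biased by design. The documents do not support that. The Abstract, the sample size section and the data collection section, read together, place those outcomes at three visits, by a masked assistant, on the same schedule in both arms. The data passed to the sample size calculation are those from the outcome measures. Bias would require therapist-elicited events to be added to the outcome counts. The article does not say that they will be, but does not exclude it. This part of the reply stands.

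A reader might also infer that the intervention arm is bound to show more events. That is too strong. The excess depends on incomplete recall, which is less likely for admissions than for minor falls. It is confined to about 19% of the observation time, and with this sample size chance can hide or reverse it.

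It can also be said that asking about harms at every contact is ordinary practice, that the safety section sets out no between-arm comparison, and that tabulation is commonly left to an analysis plan. That is fair for tabulation. But the unequal enquiry is a rule the protocol states, not a detail it leaves open.

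Two provisions might seem to fill the gap for controls, but neither does so fully. Cost evaluation has both groups report service use for the intervention period; that sets no prompt enquiry and would miss falls that led to no service use. The investigator's personal contacts are described only as a way to limit missing data. Nor does the rule on immediate notification of serious events set any interval for asking, so the conflict there is a gap in elicitation and not a contradiction.

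**Conclusion.** The point holds for adverse event records. The enquiry is unequal by a stated rule, and an unmasked therapist makes it in one arm only. Those records cannot support a fair comparison between arms and are likely to be inflated in the intervention arm whenever follow-up recall is incomplete. Under the assumed 95% weekly capture and 60-80% recall, the inflation is about 1.2-1.6 in the re-ablement period and about 1.04-1.12 over 32 weeks; with complete recall it disappears.

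The falls and admissions outcomes are at risk only if the two sources are merged. The main endpoint, feasibility, rests on screening and recruitment logs, loss to follow-up and the acceptability questionnaire, and is untouched. This is worth correcting because it is cheap and because the definitive trial may inherit the procedure. It is not an essential correction on which this trial's main conclusion depends.

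**What to change.** In Safety monitoring and adverse events:

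1. State that any between-arm comparison of falls, admissions or adverse events uses only events elicited at the three masked follow-up visits, with the same questions and recall window in both arms.
2. Record the source of each event. List those first learned at occupational therapy visits separately, as intervention-arm safety information.
3. Use the investigator's already planned personal contacts to ask both arms the same adverse event question at the same intervals during re-ablement.

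The cost is a few sentences, one source field on the case report form, and a standard question added to those contacts. The downside is that some intervention-arm events known only from treatment visits drop out of the comparative table; they are still reported in the safety listing.

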## Discussion

To our knowledge, this is the first RCT of an occupational therapy intervention in a homecare re-ablement service setting. The Social Care Institute for Excellence (SCIE) in England has highlighted, as a research priority, the comparison of outcomes for users who receive occupational therapy treatment as part of their re-ablement period with those who do not [4]. This study will provide the foundations for a further, appropriately powered study to investigate this. Therefore the findings from this study will be relevant to researchers, clinicians, commissioners and service users. The findings will also assist the development and configuration of homecare re-ablement services in the future.

We plan to disseminate our findings through presentations at national and international rehabilitation and occupational therapy conferences, and will submit findings for publication in a peer-reviewed academic journal. This study also forms part of PW’s National Institute for Health Research (NIHR) funded PhD and the findings will also be written up as part of his thesis.

## Trial status

Recruitment commenced in April 2014. The trial is registered with Clinicaltrials.gov with the ISRCTN number 21710246 (registered on 31 March 14). Recruitment is expected to finish in November 2014.

## Abbreviations

ADL: Activities of daily living
ASCOT: Adult Social Care Outcomes Toolkit
BI: Barthel index
COT: College Of Occupational Therapists
CRF: Case report form
CSI: Caregiver Strain Index
GCP: Good clinical practice
NCTU: Nottingham Clinical Trials Unit
NEADL: Nottingham Extended Activities Of Daily Living
RCT: Randomized controlled trial
REC: Research Ethics Committee
SCIE: Social Care Institute For Excellence
SF-36: Short-form 36
TSC: Trial Steering Committee.
